## Abstract

**Background:**

Worldwide, almost 50million people lived with dementia in 2016. A cure or disease modifying pharmaceutical treatment for dementia remains elusive so alternative therapies are of critical importance. Mounting evidence supports exercise in the prevention and therapy of dementia. However, the cognitive, physical, and psychological challenges common to dementia along with a poor understanding and accommodation of dementia in the community are major barriers to exercise. Consequently, effective delivery options need to be identified. The primary objective of this study is to compare the effectiveness of center-based (CB) exercise versus home-based (HB) exercise for achievement of physical activity guidelines among people with MCI or mild dementia.

**Methods:**

This is a randomized parallel-group trial comparing the effects of CB and HB exercise adherence among community-dwelling adults ≥50 years with a clinical diagnosis of MCI or mild dementia. Participants will be randomized to either CB or HB exercise. The CB group will meet weekly for small group exercise and will be prescribed additional exercise to be completed independently. Participants in the HB group will be given a physical activity prescription to be completed independently in the community. Participants in HB will also be contacted by phone monthly to adjust exercise prescriptions. The primary outcome will be achievement of exercise guidelines (150 min/wk. of moderate activity) assessed using an activity monitor. Secondary objectives will evaluate cost-effectiveness and the influence of individual and environmental factors on the primary outcome. Tertiary outcomes include physical function, cognition, mood, and quality of life.

**Discussion:**

There is scant research to indicate the most effective way to deliver exercise to people with MCI and mild dementia, which is needed specifically because these groups face significant barriers to exercise. To capitalize on the benefits of exercise, feasible exercise delivery options need to be identified. The results of this study will directly complement ongoing clinical trials and will be essential to implementing exercise recommendations specific to the prevention and therapy of dementia in a feasible and cost-effective manner when they emerge.

**Trial registration.:**

Clinicatrials.gov; Identifier: NCT02774720 (version updated December 12, 2016).

## Background

Worldwide, there were 46.8 million people living with dementia in 2016. [1] This number is expected to reach 131.5 million by 2050. [1] Since there is currently no disease modifying agent or cure for dementia, it is essential to identify alternate preventative and therapeutic approaches. Exercise is one promising strategy to prevent and treat dementia. [2] Convergent evidence from cohort studies, clinical trials, and animal models supports exercise as an intervention to improve cognitive function among older adults with and without cognitive impairment, [3] though more rigorous randomized controlled trials are still needed. [4, 5]

There is no doubt that exercise has benefits, however, for older adults with and without cognitive impairment. Exercise is recommended by the American College of Sports Medicine for older adults to improve health, functional capacity, quality of life, and functional independence. [6] A meta-analysis of exercise trials among people with cognitive impairment confirmed that exercise programs as short as 3 months improved daily function and physical function among this group. [7] Specifically, exercise improves daily function, mobility, and balance among those at risk for (with mild cognitive impairment (MCI)) or with dementia. [7–10] Accordingly, the Ontario Brain Institute (CANADA) developed consensus recommendations of 150 min per week of moderate aerobic exercise and twice weekly strength training for the prevention and therapy of dementia, [11] in line with general guidelines for older adults in many countries (for example, [12–14]).

Even with the substantial associated benefits, many older adults remain inactive, [15, 16] and people with mild cognitive impairment (MCI) and dementia are more sedentary than their peers. [17, 18] Persons with dementia and their care partners report that the cognitive, physical, and psychological challenges common to dementia (e.g., memory and attentional deficits, apathy, co-morbid health problems [19, 20]). In addition, persons with dementia typically experience a loss of freedom as cognitive impairment progresses, which means that persons with dementia may be dependent on their care partner (or others) to access both local and more distant opportunities. [21] This means that care partner support for exercise in addition to the health of and fatigue among their partners has a strong influence exercise behaviours. [21] Furthermore, a poor understanding and accommodation of dementia in the community may lead to explicit or implicit exclusion of persons with dementia from exercise programs, further reducing opportunities. [21]

Despite substantial support for exercise as a therapy for people with MCI or dementia, we have a poor understanding of the best strategies to increase exercise levels in this group. [22] Clinical trials of community-dwelling adults with MCI or dementia have primarily, [5] but not always, [23, 24] employed highly controlled, centre-based interventions which increase internal validity but poorly reflect what is available in the community. Prior comparisons of center-based [CB] versus home-based [HB] exercise programs among various patient groups and populations indicate that the relative effectiveness varies by group,[25] suggesting a need to study the effectiveness of these delivery options in unique patient groups. Moreover, a recent review specifically highlighted the need to identify effective exercise delivery options specific to people with MCI and dementia. [22]

Trials of exercise interventions among people with MCI or dementia indicate that both CB and HB exercise can be effective for improving cognitive, physical, and other outcomes (for example, [23, 26]). It is possible that the most effective option will not be uniform even within this clinical group but may depend further on the individual (e.g., degree of care partner support, diagnosis (i.e. MCI vs dementia), severity of deficits) and the context (e.g., weather, proximity to facilities). Consequently, the aim of this study is to compare the effectiveness of CB versus HB exercise programs in achieving aerobic exercise guidelines (percent of 150 min per week of moderate intensity activity) among people with MCI and mild dementia. Secondary objectives will compare the cost-effectiveness of the interventions and examine the influence of individual and environmental factors on achievement of the primary outcome. Exploratory objectives will compare the effect of CB and HB exercise on physical function, cognitive function, vascular health, quality of life, instrumental activities of daily living (IADLs), mood, and individual goal attainment. Based on prior results among healthy older adults, [27] we hypothesize that participants assigned to the HB exercise group will have a higher percent achievement of physical activity guidelines compared to the CB exercise group. Conversely, we hypothesize that the CB group will experience greater gains in physical function than the HB group.

## Methods & design

This is a pragmatic, randomized, parallel group trial to explore the relative effectiveness of two exercise delivery options (CB versus HB) among 60 people with MCI and mild dementia. The study will be conducted at two sites in Canada: Toronto (Sunnybrook Health Sciences Centre and University Health Network-Toronto Rehabilitation Institute) and Kitchener-Waterloo (University of Waterloo). Enrollment of participants began in September 2016 and is expected to continue until September 2018.

The study flow is shown in Fig. 1. Assessments will occur at baseline and immediately after the completion of the intervention. In addition to these assessments, physical activity, health status, and health care utilization will be reported monthly. Participants will be randomly assigned to CB or HB after baseline assessments, blocked by site, via a central internet randomization service (www.randomization.com). The randomization will be managed by a department research assistant not involved in the assessments and communicated to the participants directly or via the site research coordinator. Those who assess and those who analyze outcomes will remain blinded to allocation throughout and will report whether there was any indication of group allocation. In addition, analyses will be done by code (that is, Group ‘A’ and ‘B’) with code only revealed after analyses are complete. Due to the nature of the intervention, participants and exercise physiologists will not be blinded to group but participants will be blinded to the study hypotheses.

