### Participants

We will recruit people with MCI or mild dementia from both clinics and the community. Participants will be recruited from memory and geriatric clinics as well as through flyers distributed through local community centres and groups, such as the Alzheimer Society and dementia support groups. Promotion through news articles and/or advertisements will be used to supplement recruitment, where necessary. Interested individuals will be screened either in the clinic or by phone using inclusion/exclusion criteria and the Canadian Society of Exercise Physiology physical activity readiness questionnaire-plus (PAR-Q+), [27] a screen for physical activity readiness that reviews common counter-indications to exercise. A consent and screening session will be arranged for those who appear eligible and are interested.

Inclusion and exclusion criteria are purposely broad to reflect the spectrum of people with MCI and mild dementia treated in academic and community clinics. To be eligible for the study, people must: 1) have a clinical diagnosis of MCI or dementia, as determined by the treating physician as opposed to specific criteria; 2) MMSE > 22 or MoCA > 17; 3) be 50 years or older; 4) have a stable pharmaceutical regimen for at least 2 months; 5) be able to travel to the CB site; 6) have a care partner who will support at-home exercise and provide information for some assessments; 7) be able to complete a 2-min walk; 8) have adequate English to understand exercise training and assessments; 9) have adequate hearing and vision for cognitive tests; 10) be able to comply with assessment and training schedule; and 11) be screened safe for exercise by either a physician or certified exercise physiologist. People who currently participate in moderate exercise ≥3×/week or have cardiovascular, musculoskeletal, pain, or other co-morbid conditions that preclude exercise will be excluded.

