### Sample size calculation

Sample size is based on the primary objective, to detect a significant difference in percent achievement of physical activity recommendations (continuous variable) between CB and HB groups over the intervention period. A recent Cochrane review of CB versus HB among older adults indicated that HB exercise had better physical activity achievement than CB, with an effect size of 0.8. [27] There were no studies that targeted people with cognitive impairment. To account for the possibility that cognitive impairment may reduce the feasibility of HB, we used a smaller effect size of 0.6, an alpha of 0.05 and a beta of 0.85 with two-group repeated measures MANOVA (within and between factors) to estimate a sample size of 39. We assumed 35% drop out, similar to our pilot work and to a previous study of exercise in people with MCI, [54] to bring the required sample size to 60.

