The results from this trial will directly complement ongoing clinical trials regarding the efficacy of exercise to help inform implementation of emerging exercise guidelines for the prevention and therapy of dementia in a feasible and cost-effective manner. Prior studies comparing HB versus CB exercise among other populations differ in findings, suggesting the relative effectiveness may be population specific. Furthermore, it is likely that both exercise levels and the optimal method of exercise delivery will differ according to the individual’s characteristics, experiences, and circumstances as well as the environment in which they live. For example, the care partner for a person with dementia may be a primary influencer of the person’s exercise level, whether it be a positive or negative influence. Often, people with MCI or dementia will rely on their care partner for travel to exercise facilities so partners who are unsupportive or in poor health can restrict exercise opportunities outside of the home (CB exercise). In contrast, CB exercise may be more appealing if travel distances are short, so that the benefits of guided exercise outweigh the downsides of time and effort.

Study limitations should also be acknowledged. We purposely include individuals with a range of cognitive impairment and a variety of causes in order to best represent the population seen in clinical practice. However, if significant variability exists in the influence of interventions, then Type II error may occur – a lack of significant effect in our sample despite a true effect in the population. However, including a representative sample increases the generalizability of our results. In addition, we take a pragmatic approach in this study and include interventions as could be delivered in practice. This has the advantage of translating readily to ‘real-life’. The disadvantage is that the magnitude of effects may be smaller than with highly controlled interventions and the cause of differences is more difficult to determine.

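### The primary model has no term for diagnosis (MCI or dementia), although eligibility mixes the two and allocation is blocked by site only: a modest loss of precision that is cheap to recover

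*Protocol article*

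**What the plan says.** All references are to the protocol article.

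- **Allocation (Methods & design):** "Participants will be randomly assigned to CB or HB after baseline assessments, blocked by site, via a central internet randomization service". There are two sites. Block size and allocation ratio are not given.
- **Eligibility (Participants, criterion 1):** people must "have a clinical diagnosis of MCI or dementia, as determined by the treating physician as opposed to specific criteria". The criteria are described as broad on purpose. The expected split between MCI and dementia is not given.
- **Possible modifiers (Background, final paragraph):** the most effective option may depend on the individual and the context. Care partner support is listed first, then diagnosis, then severity of deficits.
- **Primary model (Analysis, Primary objective):** a mixed linear regression with group, time and group x time, plus random effects for participant and site. Diagnosis does not appear.
- **Secondary objectives (ii):** person and setting characteristics enter the same type of model as a factor. No interaction of the characteristic with group is stated.
- **Discussion (limitations):** the mixed population is defended for generalizability, with the admission that "if significant variability exists in the influence of interventions, then Type II error may occur".

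**The concern.** Diagnosis is an entry criterion, so it is known for every participant before allocation. The article itself gives reasons why it may matter: the Background describes barriers to exercise and a growing dependence on the care partner as impairment progresses. Those are reasons to expect diagnosis to affect how much activity changes over the intervention, and not only where it starts.

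The baseline measurement and the group x time term absorb a stable difference in activity between MCI and dementia. They do not absorb a difference in change. In a trial of 60, chance can leave one arm with visibly more dementia, and nothing in the stated primary analysis accounts for it. At stake are some precision, and how well the single realized result stands up if the baseline table shows such a gap.

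**Working it through.** **Inputs from the article.** Sample size calculation: "to estimate a sample size of 39", effect size 0.6, and "We assumed 35% drop out, similar to our pilot work and to a previous study of exercise in people with MCI", giving 60. Methods & design: two sites, site-only blocking.

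**Assumptions (not in the article).** 1:1 allocation; 20-50% with dementia (results are symmetric above 50%); for the simulation, 30 per site and blocks of 4; diagnosis shifts change in activity by d = 0.2 to 0.8 within-diagnosis SD.

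**The plan's own figure.** 39 / (1 - 0.35) = 60, so the inflation reproduces. The 39 reproduces as a repeated-measures MANOVA within-between test with f = 0.6, four measurements, alpha 0.05 and power 0.85. Because 0.6 there acts as Cohen's f and not as a standardized mean difference, I do not express the shifts below as a percentage of 0.6.

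**Which sample to use.** The Analysis section specifies intention-to-treat with multiple imputation, so the analysis set is the 60 randomized.

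**Chance of imbalance, exact.** With K participants with dementia among 60, the number k in one arm of 30 has

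P(k) = C(K, k) C(60 - K, 30 - k) / C(60, 30),

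and the gap between arms is |k - (K - k)| / 30. For K = 30, a gap of at least 20 points means 18 v 12 or worse.

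| Share with dementia (K) | 10 points or more | 20 points or more | 30 points or more |
|---|---|---|---|
| 20% (12) | 33.3% | 10.4% | 0.2% |
| 30% (18) | 39.9% | 15.8% | 1.0% |
| 40% (24) | 43.0% | 18.7% | 1.7% |
| 50% (30) | 43.9% | 19.6% | 1.9% |

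**Chance of imbalance, simulated with site blocks of 4** (8,000 runs each):

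| Share with dementia | 10 points or more | 20 points or more | 30 points or more |
|---|---|---|---|
| 30% | 43.4% | 10.4% | 1.3% |
| 50% | 49.1% | 13.6% | 2.4% |

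With blocks of 4 within site x diagnosis, the chance of even a 10-point gap falls to 0.01% or less.

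**Effect of a 20-point gap on the contrast.** Shift = 0.20 x d, so 0.20 x 0.2 = 0.04 SD and 0.20 x 0.8 = 0.16 SD. For scale, the simple two-sample standard error at 30 v 30 is sqrt(2/30) = 0.26 SD.

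**Variance removed by adjustment.** Share = p(1 - p)d² / (1 + p(1 - p)d²).
- p = 0.5, d = 0.2: 0.01 / 1.01 = 1.0%
- p = 0.5, d = 0.8: 0.16 / 1.16 = 13.8%
- p = 0.2, d = 0.2: 0.0064 / 1.0064 = 0.6%
- p = 0.2, d = 0.8: 0.1024 / 1.1024 = 9.3%

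At p = 0.5 the standard error falls by 1 - sqrt(0.990) = 0.5% to 1 - sqrt(0.862) = 7.2%.

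**What imbalance still costs after adjustment.** The correlation of arm with diagnosis at 18 v 12 is 0.2, so the variance of the adjusted contrast rises by 1 / (1 - 0.04) = 1.04, about 4%. Averaged over unrestricted random allocations the squared correlation is 1 / (60 - 1) = 1.7%.

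**The case against.** The strongest reply is that nothing here is invalid. Chance imbalance under proper randomization is part of the sampling error that the test and the confidence interval already cover. A shift of 0.04-0.16 SD is small beside a standard error of about 0.26 SD. Site-only blocking is defensible at N = 60, several modifiers are named, and a physician-assigned diagnosis without set criteria is a noisy stratifier. Enrolment began in September 2016, so new allocation lists would cover only part of the sample. Diagnosis may be examined under the secondary objectives, and an analysis plan that is not shown may add covariates.

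Most of this stands, and it limits the point to precision and credibility. Two parts do not dispose of it. The article states the terms of its primary model, and diagnosis is not among them; if an analysis plan already adds it together with its time interaction, the point is met. And a secondary model with the characteristic as a factor leaves the primary estimate unadjusted.

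A reader might also infer more than the documents support:

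- **That the result would be biased.** It would not be: over repeated randomization the estimator is unbiased.
- **That imbalance is likelier because only 39 are analysed.** Rounding 39 to 20 v 20 gives 34% for 20 points or more and 11% for 30 or more (half with dementia). With 20 v 19 these are 20.5% and 5.6%, and intention-to-treat with imputation keeps all 60 in any case.
- **That the article expects diagnosis to be the leading modifier.** It says only that the better option may depend on it, and lists it second.
- **That the subgroup comparison would collapse.** Cells of 18, 12, 12 and 18 in place of 15 each raise the variance of the interaction contrast from 4/15 = 0.267 to 2/18 + 2/12 = 0.278, about 4%.
- **That balancing or adjusting answers the limitation in the Discussion.** That limitation concerns variation in the effect of the interventions, which neither step tests or removes.

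**Conclusion.** The point holds as a modest improvement to a stated method, not as an error that threatens validity. A factor that the article itself names, known for everyone at entry, is in neither the allocation nor the primary model. An imbalance of 20 points or more has a chance of about 10-20% (10-14% with assumed site blocks of 4), and one of 30 points or more about 2% or less.

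The consequence depends on how strongly diagnosis affects change in activity, and the article gives no figure for that. The upper figure of 14% of variance needs both half the sample with dementia and a 0.8 SD effect. At 0.2 SD the 0.6-1.0% gain does not cover the average 1.7% cost of estimating the adjustment, so the case there rests on credibility alone.

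**What to change.** Before the group code is broken, pre-specify diagnosis (MCI or dementia, as recorded at entry) and diagnosis x time as fixed effects in the primary mixed model for all participants. Both terms are needed: the main effect alone shifts baseline and follow-up equally and would not adjust the change contrast carried by group x time. The blinded A/B coding in Methods & design makes this possible without knowledge of results.

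The cost is two extra parameters and no new data. The gain is limited by misclassification in a physician-assigned diagnosis.

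Stratifying the remaining allocations by site x diagnosis (four lists in place of two) is optional. Once the model adjusts, it saves only the roughly 4% variance penalty of a 20-point gap, reaches only participants not yet allocated, and leaves some incomplete blocks.

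If the question is whether the CB-HB effect differs by diagnosis, add a group x time x diagnosis term to the secondary analysis and state it as such.

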**Fig. 1 Fig1:**
[figure not shown]
Flow of study participants

This study has been approved by an Ethics Committee for Human Research at the University of Waterloo, Kitchener-Waterloo Tri-Hospitals, Sunnybrook Health Sciences Centre, and the University Health Network. This study has been registered at *clinicaltrials.gov* with the identifier NCT02774720 (version updated December 12, 2016).

### Participants

We will recruit people with MCI or mild dementia from both clinics and the community. Participants will be recruited from memory and geriatric clinics as well as through flyers distributed through local community centres and groups, such as the Alzheimer Society and dementia support groups. Promotion through news articles and/or advertisements will be used to supplement recruitment, where necessary. Interested individuals will be screened either in the clinic or by phone using inclusion/exclusion criteria and the Canadian Society of Exercise Physiology physical activity readiness questionnaire-plus (PAR-Q+), [27] a screen for physical activity readiness that reviews common counter-indications to exercise. A consent and screening session will be arranged for those who appear eligible and are interested.

Inclusion and exclusion criteria are purposely broad to reflect the spectrum of people with MCI and mild dementia treated in academic and community clinics. To be eligible for the study, people must: 1) have a clinical diagnosis of MCI or dementia, as determined by the treating physician as opposed to specific criteria; 2) MMSE > 22 or MoCA > 17; 3) be 50 years or older; 4) have a stable pharmaceutical regimen for at least 2 months; 5) be able to travel to the CB site; 6) have a care partner who will support at-home exercise and provide information for some assessments; 7) be able to complete a 2-min walk; 8) have adequate English to understand exercise training and assessments; 9) have adequate hearing and vision for cognitive tests; 10) be able to comply with assessment and training schedule; and 11) be screened safe for exercise by either a physician or certified exercise physiologist. People who currently participate in moderate exercise ≥3×/week or have cardiovascular, musculoskeletal, pain, or other co-morbid conditions that preclude exercise will be excluded.

